#### Sleep assessment

2.3.1

Participants will undergo a polysomnography (PSG) recording at home using a portable device (Embletta^®^ MPR Sleep System, NATUS, Orlando, United States). Ten electrodes will be placed over the scalp according to the international 10–20 system: frontal (F3 | F4), central (C3 | C4 | Cz), occipital (O1 | O2), ground (Cz | Fz), and a bi-mastoid reference (A1 | A2), with impedance kept below 15 kΩ. This montage will also include an electrooculogram (EOG), an electrocardiogram (ECG), and a chin electromyogram (EMG). Respiratory movements, airflow, and oxygen saturation will be recorded with abdominal and thoracic belts, nasal and oral thermistors, and finger pulse oximetry. The Electroencephalogram (EEG) signal will be digitized at a sampling rate of 256 Hz. High-pass and low-pass filters will be applied, respectively, at 0.3 Hz and 35 Hz. PSG recordings will be manually scored in 30-s epochs following the recommended standard criteria of the American Academy of Sleep Medicine (53) using RemLogic software. Sleep analyses will be conducted to calculate standard sleep parameters, including total sleep time (TST, min), sleep onset latency (SOL, min), wake after sleep onset (WASO, min), sleep efficiency (SE, %), percentage of time spent in each sleep stage (S1, S2, Slow-Wave Sleep, and Rapid-Eye Movement sleep, %), and apnea-hypopnea index (AHI). Sleep apnea will be defined by a ≥ 90% drop of nasal pressure for at least 10 s, whereas sleep hypopnea will be characterized by a ≥ 30% drop of nasal pressure for a minimum of 10 s, associated with an arousal or an oxygen desaturation of ≥3% (53).

Sleep quality and quantity will be evaluated using validated self-report questionnaires. Sleep quality and disturbances over the last month will be evaluated using the Pittsburgh Sleep Quality Index (PSQI) (49) through different parameters, including work, sleep habits, sleep disturbances, subjective sleep quality, the use of sleep medication, and trouble staying awake during the day. Daytime sleepiness will be assessed using the Epworth Sleepiness Scale (ESS) (54) and insomnia over the last month will be assessed with the Insomnia Severity Index (ISI) (55). Participants will complete a sleep diary to subjectively assess sleep quality and duration, including hours of bedtime, sleep quality, number, and duration of nocturnal awakenings and naps.

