### Study design

2.1

The study is a randomized controlled trial with four parallel groups: a Physical Exercise Training group (PET), a PET combined with Bright Light Exposure group (PET + BLE), a Galvanic Vestibular Stimulation group (GVS), and a control group [Health Education (HE)]. All participants will be provided written informed consent before their inclusion. The protocol has been approved by the local ethical committee (Comité de Protection des Personnes, CPP Nord Ouest III, Caen) in compliance with French regulations (trial registration number: IDRCB: 20206A01578-31). The researchers will provide participants with detailed written and oral information about the trial, ensuring voluntary participation and emphasizing that participants may withdraw at any time.

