### Participant

2.2

Participants will be recruited through advertisements in the local newspapers and media reports. One hundred healthy retired participants, both male and female, aged between 60 and 70 years and independently living in Normandy, will be enrolled. Exclusion criteria will include: not having computing equipment (computer, web connection and webcam), signs of cognitive impairment reflected by a Mini-Mental State Examination (MMSE) score below 26/30 (48), no sleep complaint reflected by a Pittsburgh Sleep Quality Index (PSQI) score > 5 (49), extreme circadian typology reflected by the Morningness-Eveningness Questionnaire (MEQ) (50) score below 31 or above 69, uncontrolled psychiatric, vestibular, neurologic, endocrine or cardiovascular affections, uncorrected hearing and/or visual impairment, psychotropic or bradicardizing medical treatments, alcohol, drug or caffeine abuse, and recent hospitalization (<30 days), all to be assessed by medical evaluations and screenings. Participants ranking moderately or highly active according to the International Physical Activity Questionnaires (IPAQ) (51) will be excluded. The ability to engage in moderate to vigorous physical activity will be assessed by a medical examination and cardiac screening during a maximal incremental test (VO_2_ peak) on a cycle-ergometer (detailed below), supervised by cardiologists at the sports medicine department of the local hospital of CHU in Caen. Complete inclusion and exclusion criteria are listed in Table 1. Eligible participants will be allocated to one of four groups using simple randomization from a computer-generated numbered sequence with 25 blocks of 4, to be conducted by researchers. Participants will be assigned a number in the order of their registration inclusion in the study.

**Table 1 tab1:** Inclusion and exclusion criteria.

Inclusion criteria	Exclusion criteria
Participant ≥60 ≤ 70 y.o Retired for ≥12 months Good health condition Living in Normandy Sedentary behavior Sleep complaints reflected by a PSQI score > 5 Computing equipment Satisfactory cardiac screening	Cognition <26/30 on the MMSE IPAQ = moderately and highly active Circadian typology = extreme chronotype Sign of cognitive impairment Uncontrolled psychiatric, vestibular, neurologic, endocrine or cardiovascular affections Uncorrected hearing and/or visual impairment Psychotropic or bradicardizing medical treatments Recent hospitalization (<30 days) Alcohol, drug or caffeine abuse

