### Assessments

2.3

Inclusion and randomization will occur at the baseline assessment (visit 1) and will involve the completion of pre-inclusion questionnaires. A pre-intervention visit will take place before the start of the intervention (visit 2) and a 12-week follow-up assessment will occur at the end of the 12-week intervention (visit 3) (Figure 1A). A final assessment will be performed after completion of the 14-week intervention, but only for control and GVS groups (visit 4) (Figure 1B). According to the literature, a typical GVS protocol is short and does not exceed 2 weeks (52). Therefore, the GVS protocol will be shorter than PET and BLE interventions to ensure participant feasibility and acceptability. The two weeks of vestibular stimulation will be scheduled after the 12-week follow-up to ensure consistent design (Figure 1B). The control group will be compared to the PET and PET + BLE group, but also to the GVS group.

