**Figure 1 fig1:**
[figure not shown]
Participant’s flow chart. **(A)** The first part of participant’s flow chart: PET and PET+BLE interventions; **(B)** the second part of participant’s flow chart: GVS intervention. PET, Physical Exercise Training; BLE, Bright Light Exposure; HE, Health Education; GVS, Galvanic Vestibular Stimulation.

Sleep, circadian rhythms, physical and motor fitness, cognitive, QoL, and mood measurements will be assessed during visits 2, 3, and 4, by researchers in our laboratory. The VO_2_ peak test will be performed during visits 2 and 3 only for PET, PET + BLE, and control groups (not for the GVS group, which will not engage in physical exercise) and will allow the exclusion of participants with cardiac disorders. These tests will be conducted by cardiologists at the sports medicine departments of the local hospital of CHU in Caen. The content of all assessments is described in Figure 1.

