#### Cognitive assessment

2.3.5

Cognitive executive functions will be evaluated using tests from the GREFEX battery (64). Inhibition will be assessed using the Stroop Color-Word Interference test (65). Mental flexibility will be assessed using the Trail Making Test (TMT) (52). The dual-task performance will be assessed using Baddeley’s dual task (66). Long-term memory will be assessed with a computerized task based on the memory game principle (67). This task, adapted from Rasch et al. (67), will evaluate the consolidation of visuospatial learning during sleep and will involve memorizing 12 pairs of cards. Learning will be considered achieved when 67% of the responses will be correct (a total of 8 pairs out of 12). A recall will be proposed the next morning after the night’s polysomnography. The number of pairs of cards correctly retrieved after learning and after the night’s sleep will be collected to calculate a rate of improvement or forgetfulness during the night.

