### Statistical analyses

2.7

Data will be analyzed with R statistical software (R Core Team, Austria). The statistical analysis will determine the effects of the three different training interventions on sleep, fitness, cognitive, and quality of life variables compared to a control group. The analysis will include subjects who completed all the pre-and post-tests. If participants drop out or deviate from the intervention protocols, their data will not be used. Deviations will include non-eligibility, withdrawal of consent, missed test visits, and intervention protocol not completed. Data from the pre-test and post-test will be presented using descriptive statistics: mean, standard deviation, and percentage to describe the participants’ characteristics and performance on assessments. Comparisons within and between four groups at baseline and post-intervention will be done using repeated measures ANOVA, after checking for normality. Assessments will be considered as the dependent variables, and the group will serve as the independent variable. *Post hoc* analyses will be conducted when a significant main effect is observed using Tukey’s test to correct for multiple comparisons.

The initial ANOVA, comparing the PET, PET, and BLE, control group, will aim to assess the presence of intervention effects (pre/post). The hypothesis is that the combined PET and light interventions will result in improved outcomes in both groups compared to the control group across various domains, including physical and motor fitness, cognitive, QoL, circadian rhythms, and sleep variables.

The second ANOVA, comparing the GVS and control groups, will be designed to assess the existence of intervention effects (pre/post). The hypothesis is that the GVS intervention will lead to improvements in balance, cognition, QoL, circadian rhythms, and sleep variables compared to the control group.

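### Section 2.7 plans tested within-group comparisons and labels pre/post change an intervention effect, although the trial is sized and hypothesised on between-group differences in change

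*Protocol article*

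**What the plan says.** All references are to the protocol article.

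- **Section 2.7, general analysis.** "Comparisons within and between four groups at baseline and post-intervention will be done using repeated measures ANOVA". Post hoc Tukey tests follow a significant main effect. The group-by-time interaction is not mentioned, and nothing says that change within a group is descriptive only.
- **Section 2.7, the two ANOVAs.** One compares PET, PET+BLE and control; the other compares GVS and control. The second "will be designed to assess the existence of intervention effects (pre/post"), and the first has an equivalent phrase. Each is followed by a hypothesis of improvement relative to control.
- **Section 2.6.** The sample size is set to detect differences between groups in pre-to-post change: Cohen's f = 0.4, alpha 0.05, power 0.90 (printed as p), 24 per group.
- **Section 2.1.** "The study is a randomized controlled trial with four parallel groups", one of them an active control.
- **Sections 2.3.1 and 2.3.5.** "Participants will undergo a polysomnography (PSG) recording at home using a portable device"; for the memory task, "A recall will be proposed the next morning after the night’s polysomnography". One night per assessment is the natural reading.
- **Sections 2.2 and 2.3.** Entry requires "Sleep complaints reflected by a PSQI score > 5". "Inclusion and randomization will occur at the baseline assessment (visit 1) and will involve the completion of pre-inclusion questionnaires". Sleep outcomes are measured at visits 2, 3 and 4. The two weeks of GVS come after the 12-week follow-up (visit 3).

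**The concern.** A pre/post test inside one arm asks whether that arm changed. It cannot say whether the intervention caused the change. Anything that moves all arms together between the two assessments enters that test in full: a time trend, or familiarity with a home recording that uses scalp electrodes, belts, thermistors and an oximeter. It cancels only when the change in one arm is compared with the change in another.

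Section 2.7 provides for comparison within groups as well as between them, attaches the term intervention effect to pre/post change, and does not name the one ANOVA term that isolates the effect. Followed literally, it would allow a report that an exercise arm improved significantly while control did not, presented as efficacy although the arms do not differ. It also leaves 2.7 out of step with the quantity for which section 2.6 sized the trial.

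**Working it through.** **1. The plan's own figure.** For a one-way ANOVA with four groups, f = 0.4 and alpha = 0.05, power comes from the noncentral F distribution with lambda = N × f². At 24 per group, N = 96 and lambda = 96 × 0.16 = 15.36, which gives power 0.912. This is the smallest group size that reaches 0.90, so the stated 24 reproduces. It is a between-group calculation.

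**2. Within-arm test under a common shift.** Inputs: n = 24 per arm (section 2.6); two-sided alpha 0.05; no intervention effect; a shift s, in SDs of the change score, shared by all arms. The documents give no value for s, so 0.2 to 0.4 is an assumption shown as a range. The test is a one-sample t test on change with 23 df and noncentrality s × √24.

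| s | noncentrality | p = P(arm significant) |
|---|---|---|
| 0.2 | 0.98 | 15.6% |
| 0.3 | 1.47 | 29.1% |
| 0.4 | 1.96 | 46.7% |

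**3. The misleading pattern.** At least one of the two exercise arms is significant and control is not. With independent arms the probability is [1 − (1 − p)²] × (1 − p):

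- s = 0.2: (1 − 0.844²) × 0.844 = 0.288 × 0.844 = 24%
- s = 0.3: (1 − 0.709²) × 0.709 = 0.497 × 0.709 = 35%
- s = 0.4: (1 − 0.533²) × 0.533 = 0.716 × 0.533 = 38%

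With no shift (p = 0.05) the same expression gives 0.0975 × 0.95 = 9%, half of it in the wrong direction for each arm.

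**4. Between-arm test under the same shift.** Simulation: 24 per arm, three arms, 10,000 runs, pre/post correlation assumed to be 0.5, so that one SD of change equals one SD of a single measurement. At shifts of 0.2 and 0.3, the within-arm test rejects in 15.7% and 29.2% of arms, in agreement with step 2. The time main effect rejects in 39% and 71% of trials. The group-by-time test rejects in 5.0% and 4.7%. Over all settings run (correlation 0.5 or 0.7, shift 0 to 0.5, three arms), group-by-time stayed between 4.7% and 5.3%.

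**5. Does selection on PSQI supply the shift?** Selection is on the visit 1 score; the pre-test is visit 2. The simulation assumed PSQI mean 5 to 7, SD 3, reliability 0.60 to 0.85 and independent errors across visits. The expected fall from visit 1 to visit 3 is 0.2 to 1.0 points, but from visit 2 to visit 3 it is 0.00. Drift after visit 2 needs screening to correlate more strongly with visit 2 than with visit 3. Drift = (r12 − r13) × excess / √(2(1 − r23)). With r23 = 0.7, the low end is (0.85 − 0.75) × 0.8 / 0.775 = 0.10 SD and the high end is (0.90 − 0.60) × 1.0 / 0.775 = 0.39 SD. None of these inputs is in the documents.

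**The case against.** The strongest reply is that the plan already judges effects against a randomised control. Section 2.7 opens by saying so, both ANOVAs contain the control arm, both hypotheses are relative to it, and section 2.6 targets between-group differences in change. On that reading, within and between merely names the two factors of a repeated measures model, pre/post names its time points, and no separate paired test per arm is planned. Tukey's correction would also apply, whereas step 2 uses an uncorrected t test.

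Much of this stands. The trial does not rest on within-arm change, and its intended comparison is the right one. But 2.7 does provide for within-group comparison, does not confine it to description, and starts post hoc tests on a main effect without naming the interaction. Tukey's correction would lower the rates in step 2, but it does not remove the shift: the arm mean has truly changed, only not because of the intervention.

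Three stronger readings might be inferred, and the documents do not support them:

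- *A single PSG night biases the trial.* One night adds noise, but it does not bias a randomised comparison. Section 2.3.1 contains no error, and the absence of a described adaptation night may only reflect a condensed article. No passage gives the size of a first-night shift.
- *Selection on PSQI > 5 guarantees apparent improvement after visit 2.* Under independent errors it produces none. It concerns a questionnaire in any case, since nobody is selected on PSG. It is at most a secondary contributor that depends on assumptions.
- *Every arm is exposed to a visit 2 to visit 3 artefact in its treatment window.* Stimulation in the GVS arm starts after visit 3, so that argument should not be applied to it.

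A count of trials in which any of three arms improves would also overstate the harm, because improvement in control is not an efficacy claim.

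**Conclusion.** The point holds as an inconsistency in section 2.7 with a real consequence if the section is followed as written. Within-arm tests do not hold a 5% error rate for an intervention effect once any shift is shared by the arms: about 16%, 29% or 47% of arms at an assumed 0.2, 0.3 or 0.4 SD of change. The pattern of an exercise arm significant with control not then arises in about 24%, 35% or 38% of trials. These figures assume 24 per arm, independent arms, no multiplicity correction, and a shift whose size the documents do not supply. That the between-arm test stays near 5% does not depend on the size of the shift. The design and the randomised comparison are unaffected. The change is worth making before analysis because it brings 2.7 into line with 2.6.

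**What to change.** In section 2.7:

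1. Define the intervention effect as the between-arm difference in pre-to-post change, tested by the group-by-time interaction or by a baseline-adjusted contrast. Use this in place of the pre/post label in both ANOVA paragraphs.
2. Name the contrasts: PET versus control, PET+BLE versus control, PET+BLE versus PET, and GVS versus control. Make follow-up comparisons depend on that test of differential change, not on an unspecified main effect.
3. Remove within-group comparison as a tested analysis. Report each arm's change descriptively, as mean and 95% CI without a p-value.

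This is a matter of a few sentences, with no new data, visits or PSG nights. The cost is the loss of within-arm p-values.

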#### Galvanic vestibular stimulation (GVS)

2.4.3

Galvanic Vestibular Stimulation (GVS) is a non-invasive method used to stimulate the vestibular system. The GVS paradigm involves the bilateral bipolar mode, with the anode electrode placed on the mastoid bone behind one ear and the cathode electrode behind the other ear.

Bipolar galvanic stimulations will be delivered by the mini-CT portable box (Soterix Medical^®^, United States). Participants will self-administer five sessions per week at home (from Monday to Friday) over 2 weeks, each lasting 20 min. The intensity will be set to 1 mA, initiated by a 60-s ramp-up and terminated by a 60-s ramp-down (52). Each session will be scheduled at the same time in the morning.

The researcher will program the GVS device before the intervention, configuring it according to the specified parameters and generating 10 unique session codes for each participant, corresponding to the 10 stimulation sessions. Throughout the intervention, participants will be instructed to enter only the code assigned to the day’s session. The quality of skin-electrode contact will be systematically checked, and if the signal is deemed “poor,” the stimulation will not initiate. The electrodes will be pre-soaked in saline solution, to minimize cutaneous sensations. The first vestibular stimulation session will be conducted in the laboratory with the experimenter, after which participants will be guided to self-administer subsequent sessions at home. The intervention will be remotely monitored through the SAPATIC digital platform.

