### Sample size calculations

2.6

The sample size calculation has been performed using R statistical software (R Core Team). In order to detect relevant differences between groups in the changes from pre-to post-intervention, we determined a sample size sufficient to detect medium effect sizes (Cohen’s *f* = 0.4). Therefore, α = 0.05, and *p* = 0.90, were selected to favor clinically significant effect sizes. The sample size calculation is based on sleep quality as the main variable. A total of 24 participants per group are necessary to examine the hypothesis that interventions impact sleep quality. Two additional participants are included to compensate for possible drop-outs. Each of the four groups will consist of 25 participants, resulting in a total of 100 participants.

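### PSQI and ISI look back one month but GVS lasts two weeks, so at visit 4 about half of the recalled period precedes stimulation and both scales understate any GVS effect

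*Protocol article*

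**What the plan says.** All quotations are from the protocol article.

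- **Recall period** (Sleep assessment): "Sleep quality and disturbances over the last month will be evaluated using the Pittsburgh Sleep Quality Index (PSQI"; and "insomnia over the last month will be assessed with the Insomnia Severity Index (ISI". No shorter version is mentioned for any comparison.
- **Length of GVS** (Galvanic vestibular stimulation): "Participants will self-administer five sessions per week at home (from Monday to Friday) over 2 weeks, each lasting 20 min".
- **Start of GVS** (Assessments): "The two weeks of vestibular stimulation will be scheduled after the 12-week follow-up to ensure consistent design".
- **GVS post-test** (Assessments): "A final assessment will be performed after completion of the 14-week intervention, but only for control and GVS groups (visit 4". The text under Figure 1 adds: "Sleep, circadian rhythms, physical and motor fitness, cognitive, QoL, and mood measurements will be assessed during visits 2, 3, and 4".
- **Analysis** (Statistical analyses): "The second ANOVA, comparing the GVS and control groups, will be designed to assess the existence of intervention effects (pre/post". It does not say whether the pre-test is visit 2 or visit 3.
- **Planning effect** (Sample size calculations): a size "sufficient to detect medium effect sizes (Cohen’s *f* = 0.4", with alpha 0.05, 0.90 (printed as p, read here as power) and 24 per group. The main variable is sleep quality, with no instrument named.

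**The concern.** One pair of questionnaires serves two comparisons with very different treatment lengths. For the two exercise arms, the month before visit 3 lies wholly inside the 12-week intervention, so the recall period fits. For GVS, the month before visit 4 reaches back well before the first stimulation. Answers about those earlier nights cannot reflect GVS, yet they enter the score.

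The effect of GVS on sleep quality is one of the two stated aims and has its own ANOVA. The PSQI is the questionnaire the protocol describes as measuring sleep quality, and the Discussion cites a fall in ISI after GVS as preliminary evidence. A null result on either scale would not distinguish an ineffective stimulation from a month that was about half untreated. A later analysis cannot repair this, because a one-month answer cannot be split into its two halves.

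**Working it through.** **1. The plan's own sample size.** For a one-way ANOVA with k groups of n, power comes from the noncentral F with λ = f² × k × n. With f = 0.4, k = 4, n = 24: λ = 0.16 × 96 = 15.36 and power = 0.912. At n = 23, power is 0.898. So 24 is the smallest n reaching 0.90, and the stated figure reproduces as a four-group test.

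**2. Undiluted starting point for GVS versus control.** With two equal groups d = 2f = 0.8. A two-sided two-sample t-test at 0.05 with n = 24 per arm has noncentrality 0.8 × √(24/2) = 2.77 and power 77% (79% at 25 per arm). This is the reference for what follows.

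**3. Share of the recalled month under stimulation**, assuming visit 4 directly follows week 14:

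| Recall period | Share under GVS | Share before GVS |
|---|---|---|
| 28 days | 14/28 = 50% | 50% |
| 30 days | 14/30 = 47% | 53% |
| 31 days | 14/31 = 45% | 55% |

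Ten Monday-to-Friday sessions span 12 calendar days. Counting only those, the share is 12/30 = 40%.

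**4. Recorded effect and power at 24 per arm**, for a true d = 0.8 present from the first session:

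| Assumption about recall | Recorded d | Power |
|---|---|---|
| Nothing lost | 0.80 | 77% |
| 75% of the effect recalled (recent nights weigh more) | 0.8 × 0.75 = 0.60 | 53% |
| Even averaging, 28 days, SD unchanged | 0.8 × 14/28 = 0.40 | 27% |
| Even averaging, 30 days, SD unchanged | 0.8 × 14/30 = 0.37 | 24% |
| Even averaging, 31 days, SD unchanged | 0.8 × 14/31 = 0.36 | 23% |

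**5. Overlap of the visit 3 and visit 4 windows.** Two 30-day windows ending 14 days apart share 30 − 14 = 16 days. If visit 3 is the pre-test, its window contains no stimulated days and the visit 4 window contains 14 of 30. The expected change is therefore 14/30 of the effect, which is exactly the dilution in step 4 and not a second loss.

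The shared nights also reduce the noise in the change score. In the limiting case where independent night-to-night variation is the only noise, the SD of change shrinks by √(14/30) = 0.683. The recorded d is then 0.8 × (14/30)/0.683 = 0.55, with power about 46%. If visit 2 is the pre-test, the windows do not overlap.

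**The case against.** The tempting stronger reading is that the GVS effect on PSQI and ISI is simply halved. The documents do not establish that. It needs three conditions they do not give: answers that average evenly over the month, full effect from the first session, and visit 4 directly after week 14. Recall that favours recent nights loses less; gradual onset loses more. The 24% power figure also holds the SD fixed, and step 5 shows it can be about 46% for a change from visit 3. This part of the objection stands, so the size is given as a range.

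A reader might also infer that the main GVS endpoint is compromised. The protocol does not name the PSQI as the instrument behind sleep quality in the sample size section. It calls polysomnography a gold standard and also has the sleep diary assess sleep quality. Polysomnography, actigraphy and the diary have no stated one-month window, and sleep and circadian measures are repeated at visit 4. A GVS effect can therefore still be seen in this trial, and the bias cannot create a false benefit. This also stands.

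Nor can the alternative measures be assumed to fall inside the stimulation weeks. The protocol places visit 4 after the course and dates neither the seven actigraphy days nor the diary days. Their placement has to be fixed.

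The timing mismatch itself survives: it follows from the stated recall period, course length and visit order, whatever is assumed about recall.

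**Conclusion.** The concern holds for PSQI and ISI in the GVS versus control comparison only. With visit 4 directly after week 14, about 50 to 55% of the recalled period precedes stimulation, and both scales understate any GVS effect. For a true d = 0.8 at 24 per arm, power falls from 77% to about 53% if three quarters of the effect is recalled, and to about 24% under even averaging of a 30-day month with an unchanged SD. The direction is firm as long as stimulation does not alter recall of nights before it. The size is a model result, not a figure from the protocol. The 12-week exercise comparison is unaffected. This is a worthwhile, inexpensive correction to how the GVS result is judged, not a defect that leaves the comparison without a usable sleep measure.

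**What to change.** For GVS versus health education:

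1. Base the sleep-quality conclusion on measures already collected that have no one-month window: polysomnography, 7-day actigraphy and the sleep diary.
2. State that the visit 4 actigraphy and diary days fall in the stimulation weeks or immediately after the last session, on the same calendar in both arms.
3. Label PSQI and ISI as supportive for this comparison, and say in advance that a null result on them will not be read as absence of a GVS effect.

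Keep the standard PSQI and ISI for the 12-week exercise comparison.

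No new measurement, participants or change to the intervention is needed. The downside is that the subjective sleep-quality measure for GVS (the diary) differs from the one used for exercise training, so the two results cannot be set side by side on one scale. Rewording PSQI and ISI to a two-week recall at visits 3 and 4 is possible, but it departs from the validated forms and loses direct comparability with visit 2. The fix does not depend on it.
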